## Abstract

**Background:**

Low serum levels of major lipid markers have been proved to be significantly associated with increased risks of hemorrhagic stroke (HS) and cerebral microbleeds (CMBs). However, there is no lipid modification guideline telling us how to maintain a balance between the prevention of ischemic stroke recurrence and the prevention of hemorrhagic events, especially in patients with acute ischemic stroke (AIS) and CMBs.

**Aim:**

The Intracranial **H**emorrhage **R**isk of Intensive **S**tatin **T**herapy in Patients with **A**cute **I**schemic **S**troke combined with **C**erebral **M**icrobleeds (**CHRISTMAS**) trial evaluates the risk of intracranial hemorrhage (i.e., HS and CMBs) of high-dose statin therapy in patients with AIS combined with CMBs.

**Methods and design:**

This is an investigator-initiated, multicenter, prospective, randomized controlled clinical trial design. Up to 344 eligible patients will be consecutively randomized to receive high-dose or low-dose atorvastatin in 1:1 ratio in 5 stroke centers in China.

**Outcomes:**

CHRISTMAS trial has co-primary outcomes, namely, hemorrhage risk: the incidence of HS and the changes in degree of CMBs until the end of 36-month follow-up.

**Discussion:**

The primary hypothesis of this study is that an excessive reduction in serum lipid levels by an intensive statin therapy in AIS patients with CMBs can increase the risk of intracranial hemorrhage. This study will shed light on new clinical decisions regarding the long-term serum lipid management in these patients with dilemma in clinical practice.

**Clinical trial registration:**

Clinicaltrials.gov, identifier: NCT05589454.

## Introduction

Cerebral microbleeds (CMBs) are a crucial radiological marker of cerebral small vessel disease (CSVD) (1) to illustrate the micropathology of perivascular hemosiderin deposition corresponding to past small foci of bleeding (2). The prevalence of CMBs increases with age and exceeds 20% in community population over 60 years old (3, 4). More importantly, CMBs are also a common comorbidity of stroke, brain trauma, Alzheimer's disease, and cerebral amyloid angiopathy (5, 6), and are associated with cognitive impairment, psychiatric symptoms, and decline of daily living ability (7).

CMBs have been identified to be indicative of bleeding-prone microangiopathy for their dynamical accumulation over time, with the burden (presence and number) of baseline CMBs predicting the development of new CMBs in both deep and lobar regions, and may predict spontaneous intracranial hemorrhage (ICH) (8–12). These pieces of evidence have suggested an important link between the presence of CMBs and future macrobleeding. However, CMBs have also been demonstrated in approximately one-third of patients with ischemic stroke (IS), that are associated with an increased risk of recurrent IS, symptomatic ICH and death (13). As the burden of CMBs in IS patients increased, the relative and absolute risk ratios for ICH increase steeply, although the absolute incidence of recurrent IS is consistently higher than that of ICH (13–16). Therefore, it raises clinical dilemmas, particularly regarding the safety of secondary prevention treatment of IS with concomitant presence of CMBs.

Statins have been widely used for secondary prevention of IS. The Stroke Prevention by Aggressive Reduction in Cholesterol Levels (SPARCL) study had proposed that the reduction in the risk of IS was primarily related to the extent to which low-density lipoprotein cholesterol (LDL-C) levels are lowered instead of statin use (17). It was the first to demonstrate that 80 mg of atorvastatin per day reduced the overall incidence of strokes and cardiovascular events in patients with recent stroke or transient ischemic stroke (TIA) and without known coronary heart disease (17). However, the correlation between statin use of an intensive dose and ICH risk has not been elucidated so far (18–20). A recent meta-analysis on intensive LDL-C-lowering statin-based therapy also revealed an increased risk of ICH related to high-dose statins (17, 21), while other studies did not show the similar conclusions that statin use (22) or intensive reduction of LDL-C (23) increased the ICH risk. More importantly, none of these previous studies have explored the relationship between intensive statin therapy and hemorrhage risk from the perspective of CMBs.

However, it is worth noting that low levels of serum triglycerides (TG), total cholesterol (TC), and LDL-C have been proved to be significantly associated with increased risks of hemorrhagic stroke (HS) and CMBs (17, 19, 24). Thus, the risk of hemorrhagic events appears to depend on the reduction extent and degree of blood lipid levels rather than on statin use *per se* (17–22, 24). Unfortunately, the current international guidelines on lipid modification are all committed to emphasize the intensive reduction for LDL-C to prevent ischemic events, with no instructions on a more propriate target range to balance the prevention of ischemic stroke recurrence and the prevention of hemorrhagic events, especially for patients requiring high-dose statin treatment. Therefore, it is of great scientific and practical significance to conduct prospective studies to reveal the clinical and neuroimaging characteristics of CMBs in acute ischemic stroke (AIS) patients, and to explore the correlation between intensive lipid-lowering therapy and hemorrhage risk.

## Methods

### Study design

The CHRISTMAS trial is a multicenter, prospective, randomized controlled trial design. Participants will be enrolled in five hospitals from two provinces in China (Sichuan and Chongqing). This investigator-initiated clinical trial will be conducted in adherence to the Good Clinical Practice guidelines and in compliance with the Declaration of Helsinki, including all revisions. The study has been approved by the ethics committee of Sichuan Academy of Medical Sciences & Sichuan Provincial People's Hospital (SAMS & SPPH) and all participating centers, and has been registered at Clinicaltrials.gov with the identifier: NCT05589454 (Supplementary material 1). Written informed consent from eligible patients or their legally authorized representatives will be obtained before patient enrollment.

### Participants

By December 2023, 344 patients will have been enrolled. The inclusion and exclusion criteria are provided in Table 1. Briefly, patients are eligible if they (1) have a non-cardioembolic ischemic stroke within 14 days from the onset of the symptoms prior to the study participation; (2) are between the ages of 18 and 90; and (3) have the presence of CMBs (without differentiating the number or localization) on baseline susceptibility-weighted imaging (SWI) (Supplementary material 2). Key exclusion criteria include active hemorrhagic diseases, hemorrhagic tendency, severe stroke, or other severe conditions that are not eligible for clinical trials. In addition, patients who have contraindications to statins or need for intravenous thrombolysis, interventional therapy, anticoagulation, or dual antiplatelet therapy shall be excluded.

**Table 1 T1:** Inclusion and exclusion criteria.

**Inclusion criteria**
1. Patients with a non-cardioembolic ischemic stroke within 14 days prior to entry to the study.
2. Adults between the ages of 18 and 90.
3. Patients with CMBs on baseline SWI imaging.
4. Patients or their legal representatives volunteer to participate and sign written informed consent.
**Exclusion criteria**
1. Patients with severe ASI (NIHSS score ≥21).
2. Patients with coma (GCS score < 8).
3. Patients with previous moderate to severe dependence (mRS score 3–5).
4. Patients with any contraindications to CT and MRI (such as metal implants, claustrophobia, etc.).
5. Patients who are allergic to atorvastatin or excipients.
6. Patients with intracranial hemorrhagic diseases confirmed by CT or MRI, such as cerebral hemorrhage, epidural hematoma, subdural hematoma, ventricular hemorrhage, subarachnoid hemorrhage, traumatic cerebral hemorrhage, or hemorrhagic conversion of infarcts, etc.
7. Patients within 6 months after hemorrhagic stroke.
8. Patients with hemorrhagic tendency, such as abnormal coagulation function, Henoch-Schonlein purpura, platelet count < 100 × 10^9^/L or abnormal platelet function, etc.
9. Patients who are ready to undergo or have undergone intravenous thrombolysis after the onset of the disease or who require urgent or recent (within 90 days) endovascular treatment.
10. Patients with severe hypertension (systolic blood pressure ≥185 mmHg or diastolic blood pressure ≥110 mmHg) that has not been controlled by treatment.
11. Patients with hypoglycemia (< 2.7 mmol/L) or hyperglycemia (>22.2 mmol/L).
12. Patients with previous cerebral arteritis, brain tumor, cerebral parasitic disease, cerebral arteriovenous malformation, cerebral cavernous hemangioma, cerebral aneurysm, severe craniocerebral injury, or intracranial infection.
13. Patients with previous severe valvular heart disease, atrial fibrillation, acute myocardial infarction, or interventional therapy in the past 6 months, heart failure (patients classified as class III-IV according to the NYHA) or patients with indications for pacemaker placement but without pacemaker installation or other malignant arrhythmias.
14. Patients contraindicate to antiplatelet therapy.
15. Patients who must use other types of statins or other types of lipid-lowering drugs such as ezetimibe.
16. Patients with severe mental disorders, or dementia that are unable or unwilling to cooperate.
17. Patients with active liver disease or unexplained two or more abnormal liver function tests [(ALT) or (AST) ≥ 3.0 × (ULN)].
18. Patients with myositis, myopathy, rhabdomyolysis, or two or more episodes of unexplained serum [CK] elevation [(CK) ≥ 5.0 × ULN].
19. Patients with other serious systemic or organic diseases that investigators believe will not allow evaluation of efficacy or are unlikely to complete the expected course of treatment and follow-up (e.g., malignancy, life expectancy < 3 years, etc.).
20. Women who are pregnant, breastfeeding, or planning to become pregnant and who do not want to use contraception.
21. Patients who enrolled in other clinical trials during the 3 months prior to the study.
22. Patients deemed ineligible for clinical trial participation by the investigator.
23. Patients or their legal representatives do not consent to participate in this study.

AIS, acute ischemic stroke; ALT, alanine aminotransferase; AST, aspartate aminotransferase; CK, creatine kinase; CT, computed tomography; CMBs, cerebral microbleeds; GCS, Glasgow Coma Scale; mRS, modified Rankin Scale; NIHSS, National Institutes of Health Stroke Scale; NYHA, New York Heart Association; SWI, susceptibility weighted imaging; TIA, transient ischemic attack; ULN, upper limit of normal.

### Randomization and blinding

All patients who are undergoing an AIS will be screened timely according to inclusion and exclusion criteria by a qualified investigator of each center. Then the eligible patients will be randomized into high-dose and low-dose atorvastatin arms in a 1:1 ratio (Figure 1). The concealment of allocation will be performed using sealed envelopes with numbers by the participants' physicians. Considering the non-subjective nature of the primary outcomes, as well as the reason that the investigator-initiated clinical trial without technical and financial support from any pharmaceutical manufacturer to develop placebos that meet the study design requirements in clinical practice, the study finally gave up the design and application of placebo, and only designed a single-blind manner for the study investigators. So, it's important to note that neither the participants nor their physicians conducting the drug intervention can be blind to the grouping, because the number of tablets administered in different groups will be different, so these physicians cannot be involved in the research process. All investigators and data collectors will not participate in the whole intervention.

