### Outcomes

#### Primary outcomes

The trial has co-primary outcome, namely, hemorrhage risk.

The first part is the incidence of HS confirmed by brain computed tomography (CT) or magnetic resonance imaging (MRI).

The second part is the changes in degree of CMBs until the end of 36 month follow-up.

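### The arm comparisons as written do not use baseline CMB degree, although the article calls CMB burden prognostic for both co-primary outcomes; adjusting for it is a nearly free gain in precision and credibility

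*Protocol article*

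**What the plan says.** - **Allocation** (Methods, Randomization and blinding): "Then the eligible patients will be randomized into high-dose and low-dose atorvastatin arms in a 1:1 ratio", and "The concealment of allocation will be performed using sealed envelopes with numbers by the participants' physicians". The article does not describe how the sequence is generated, and it names no strata, blocks or minimisation. It also does not say that allocation is unstratified.
- **Centres** (Study design): "Participants will be enrolled in five hospitals from two provinces in China".
- **Eligibility** (Participants): patients qualify if they "have the presence of CMBs (without differentiating the number or localization) on baseline susceptibility-weighted imaging (SWI"). The baseline scan is therefore read for CMBs before allocation.
- **Prognosis** (Introduction): the article describes CMBs as accumulating over time, "with the burden (presence and number) of baseline CMBs predicting the development of new CMBs in both deep and lobar regions". It adds: "As the burden of CMBs in IS patients increased, the relative and absolute risk ratios for ICH increase steeply".
- **Co-primary outcomes** (Primary outcomes): "The first part is the incidence of HS confirmed by brain computed tomography (CT) or magnetic resonance imaging (MRI"), and the change in CMB degree up to 36 months.
- **Analysis** (Statistical analysis): counts of hemorrhagic stroke (HS), and of patients by CMB grade at baseline and each yearly visit, are compared between arms by chi-square or Fisher's exact test. Time-to-event outcomes use Kaplan-Meier and log-rank. Cox regression is conditional on need, with unnamed covariates adjusted as sensitivity analyses. A generalized linear mixed model relates CMB degree to serum lipids; it is not presented as an arm comparison adjusted for baseline.

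**The concern.** The article identifies a strong baseline predictor of both co-primary outcomes, admits its full range, and measures it before allocation. The comparisons it then sets out do not use it. Two things are given up.

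The first is precision: variation between patients that baseline burden would explain stays in the error term.

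The second is protection in the one trial that will be run. If one arm happens to receive more high-burden patients, the headline comparison carries that difference, and the adjusted result is only a secondary analysis with covariates still to be chosen.

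This matters most for CMB degree. The outcome is defined as change, but the stated test compares how many patients are in each grade at each visit. CMBs mark past bleeding and accumulate, so a baseline difference in grade largely persists into the follow-up comparison.

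**Working it through.** **1. The plan's own figure.** Inputs from Sample size estimates: 25.2% vs 12.0%, two-sided 5%, 80% power. With mean rate 0.186 and difference 0.132:

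n = [1.96·√(2·0.186·0.814) + 0.8416·√(0.252·0.748 + 0.120·0.880)]² / 0.132² = 135.2, so 136 per arm (stated: 137). Allowing 20% loss, 137/0.8 = 171.25, so 172 per arm and 344 in total. The figures reproduce and are not in dispute.

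**2. Chance imbalance in burden.** The article gives no prevalence of high burden; q = 20–30% is assumed. Simple 1:1 allocation is also assumed, because the article does not state the method. SD of the between-arm difference = √(2q(1−q)/172).

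| q | SD | 95% range | P(gap ≥ 5 points) |
|---|---|---|---|
| 0.20 | 4.3 points | ±8.5 points | 25% |
| 0.30 | 4.9 points | ±9.7 points | 31% |

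Among 137 completers per arm the last column becomes 30% and 37%. Over a wider range of q (10–50%, 172 per arm) it runs from 12% to 35%.

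**3. Effect on HS.** The article gives no risk ratio R for high vs low burden; 3 to 5 is assumed. With no treatment effect and an imbalance d at the 95% limit, the spurious risk ratio is [1 + (q + d/2)(R − 1)] / [1 + (q − d/2)(R − 1)]:

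- q = 0.3, R = 3: 1.697/1.503 = 1.13
- q = 0.3, R = 5: 2.394/2.006 = 1.19
- q = 0.2, R = 5: 1.969/1.631 = 1.21

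The design ratio is 25.2/12.0 = 2.1. With a 12% overall control rate, R from 2 to 5 and q from 20% to 50%, the shift at the 95% limit is 0.9 to 2.3 points, or 6–17% of the planned 13.2-point difference.

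**4. Effect on CMB degree.** Assume 137 per arm, 20% of lower-burden patients move to high burden in either arm, and none move back. The follow-up proportion is P = q + 0.2(1−q), so a baseline gap d becomes a follow-up gap of 0.8d. The unadjusted SE is √(2P(1−P)/137).

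- q = 0.2: P = 0.36, d = 9.5 points, follow-up gap 7.6 points, SE 5.8 points. The test statistic is centred at 1.31 instead of 0.
- q = 0.3: P = 0.44, d = 10.9 points, follow-up gap 8.7 points, SE 6.0 points. It is centred at 1.45.

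Given the baseline split, the statistic has SD 0.75 and 0.67, being √[0.16(1−q)/(P(1−P))]. The chance of |Z| > 1.96 without any treatment effect is then about 19% and 22%. These are conditional on an imbalance at the 95% limit; averaged over all allocations the rate remains 5%.

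**5. Precision.** Under the same assumptions, variance conditional on baseline relative to unadjusted variance is 0.16(1−q)/[P(1−P)]: 0.128/0.2304 = 0.56 and 0.112/0.2464 = 0.45. Conditioning on baseline would remove roughly 44–55% of the variance in this simplified two-grade case.

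**The case against.** Several stronger readings are tempting, and the document does not support them.

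- **That allocation is a single unstratified list with balance left to chance.** The article gives a ratio and a concealment device and no more. Envelopes at five hospitals are compatible with separate centre lists, and a condensed article commonly leaves strata and blocks to the full protocol.
- **That the centres differ in imaging or background care.** The article does not say so. It recommends guideline-based care in both arms, and imaging is referred to a supplement not shown.
- **That burden drives both outcomes, and that imbalance moves them the same way.** The wording is that burden predicts new CMBs and may predict spontaneous ICH. A patient already in the top grade cannot worsen on the scale, so excess burden could even reduce measured worsening. This limits any claim about direction, but it is also a reason to condition on baseline grade.
- **That the trial is biased or its type I error inflated.** Unstratified randomisation is valid, and the 5% level already covers chance imbalance.

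It can also be said that the plan tests baseline balance, reviews it at the interim analysis and allows adjusted Cox models. A material imbalance would therefore be seen and examined, but none of these steps changes the primary comparison. The SAP, not shown, may settle the covariates. The point rests on what the article does state: first-line tests without adjustment, and adjustment confined to sensitivity analyses.

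**Conclusion.** The point holds as an improvement to the analysis, not as an error that invalidates the design. The article describes baseline CMB burden as prognostic for both co-primary outcomes but sets out comparisons that ignore it.

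For HS the consequence is modest. For CMB degree it is greater, because the stated comparison does not condition on the baseline grade from which change is measured. The sizes rest on assumed prevalence, risk ratio and progression, and on simple allocation. If the allocation is already stratified by burden, the imbalance figures largely disappear, but the precision argument remains, and the analysis should then reflect the strata.

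**What to change.** Before any unblinded analysis, make baseline CMB degree, on the mild-to-severe grading already in use, and centre prespecified factors in the primary comparison:

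- **HS:** log-rank test stratified by baseline degree and centre, or Cox regression with both factors.
- **CMB degree:** an ordinal or mixed model of follow-up degree by arm, adjusted for baseline degree and centre.
- Keep the unadjusted chi-square, Fisher and log-rank results as supportive, and fix in advance how sparse grades or centres are merged.

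The cost is a change to the analysis text. It needs no further patients, scans or data, and it remains possible after enrolment closes. If the SAP already says this, the article needs only to be aligned with it.

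Separately, state how the sequence is generated. If the full protocol does not stratify and patients remain to be randomised, stratifying by baseline CMB degree and centre is an option with a real drawback. Five centres by two burden levels gives ten strata averaging about 34 patients (344/10). With unblinded physicians handling the envelopes, blocks in small strata make the next allocation easier to guess. Varying block sizes reduce that risk but do not remove it. The adjusted analysis does not depend on this step.

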**Figure 1 F1:**
[figure not shown]
Design of the CHRISTMAS trial. AIS, acute ischemic stroke; CK, creatine kinase; CT, computed tomography; CMBs, cerebral microbleeds; DWI, diffusion weighted imaging; ECG, electrocardiograph; FBG, fasting blood-glucose; FLAIR, fluid-attenuated inversion-recovery sequency; GCS, Glasgow Coma Scale; mRS, modified Rankin Scale; HbAlc, glycosylated hemoglobin; HCY, homocysteine; NIHSS, National Institutes of Health Stroke Scale; PVS, perivascular spaces; SWI, susceptibility weighted imaging; TIA, transient ischemic attack; U-HCG, urine human chorionic gonadotropin; ULN, upper limit of normal; WMH, white matter hyperintensities.

### Treatment

High-dose atorvastatin arm: Atorvastatin calcium tablets four pills (80 mg), quaque nocte (24 ± 1 h between two doses), orally, until the end of follow-up.Low-dose atorvastatin arm: Atorvastatin calcium tablets one pill (20 mg), quaque nocte (24 ± 1 h between two doses), orally, until the end of follow-up.

It is strongly recommended in both arms for the optimal treatment including acute treatment and other secondary prevention agents in accordance with clinical practice guidelines and the best medical conditions in the health care unit.

### Follow-up

Detailed follow-up schedules and procedures are provided in Figure 1. Baseline characteristics, SWI and clinical laboratory tests will be obtained at enrollment. The following assessments will be performed at 1 month and annually follow-up: blood tests, SWI, study compliance, concomitant medication, adverse events, and withdrawal criteria. As it is not clear whether participants in this study would benefit more from following current guidelines or moderately relaxed lipid management targets. No further interventions which might violate the study protocol should be taken (such as suggesting withdrawal from the study or adjusting the treatment plan, etc.) if it is found that the serum lipid levels of the participants do not meet the current guidelines either for both groups. But the participants' doctor should be informed to strictly monitor their lipid levels and clinical conditions.

### Outcomes

#### Primary outcomes

The trial has co-primary outcome, namely, hemorrhage risk.

The first part is the incidence of HS confirmed by brain computed tomography (CT) or magnetic resonance imaging (MRI).

The second part is the changes in degree of CMBs until the end of 36 month follow-up.

